# Clinical research on the efficacy and safety of thread-embedding acupuncture for treatment of herniated intervertebral disc of the lumbar spine: a protocol for a multicenter, randomized, patient–assessor blinded, controlled, parallel, clinical trial

**DOI:** 10.1186/s13063-018-2864-4

**Published:** 2018-09-10

**Keywords:** Thread-embedding acupuncture, Lumbar herniated intervertebral disc, Lumbar disc herniation, Lower back pain, Radiculopathy

## Abstract

**Background:**

A lumbar herniated intervertebral disc (LHIVD) is a common problem that usually causes lower back pain and neurological symptoms that manifest as radiating pain. Several studies have reported that thread-embedding acupuncture (TEA) is effective in the treatment of LHIVD. However, these studies were of low quality and there is therefore little clinical evidence for the effectiveness of TEA in this regard. The aim of the present study is to establish the clinical evidence regarding the efficacy and safety of TEA in the treatment of pain, function, and quality of life in patients with LHIVD. The study uses a rigorously designed, full-scale, randomized clinical trial (RCT) protocol.

**Method/design:**

This is a multicenter, randomized, patient–assessor blinded, sham-controlled trial with two parallel arms. Seventy patients with LHIVD who have lower back pain more severe than 40 mm on the 100-mm visual analogue scale (VAS), and who are aged 19–70 years, will be recruited and randomly allocated to a TEA group and sham TEA (STEA) group. Both groups will receive treatment on 23 predefined acupoints once a week for eight weeks; needles with the thread removed will be used in the STEA group, while normal TEA will be employed in the TEA group. Changes in the 100-mm VAS for lower back pain after eight weeks will be assessed as the primary outcome. Furthermore, the 100-mm VAS for radiating pain, Oswestry Disability Index, Roland–Morris disability questionnaire, EuroQol 5 Dimensions 5 Levels, and global perceived effect will be measured and analyzed as secondary outcomes. All outcomes will be assessed at baseline and at 4, 8, 12, and 16 weeks after screening.

**Discussion:**

The results of this trial will help to establish the clinical evidence regarding TEA in the treatment of patients with LHIVD.

**Trial registration:**

ClinicalTrials.gov, NCT03236753. Registered on August 2, 2017.

Clinical Research Information Service of the Republic of Korea, KCT0002439. Registered on August 1, 2017.

**Electronic supplementary material:**

The online version of this article (10.1186/s13063-018-2864-4) contains supplementary material, which is available to authorized users.

## Background

A lumbar herniated intervertebral disc (LHIVD) is a common problem leading to lower back pain and neurological symptoms, including radiating pain in the lower extremities [1]. After other diseases are ruled out, such as lumbar stenosis, spondylolisthesis, and fracture, approximately 85% of patients suffering from lower back pain and radiculopathy are found to have an LHIVD [2]; the annual incidence is five per 1000 adults [3].

Depending on the severity of the neurological deficit, either surgical or conservative treatments may be considered [4]. Conservative methods, such as non-steroidal anti-inflammatory drugs, epidural injections, physical therapy, and alternative treatments are appropriate for most patients who do not have severe neurological symptoms [5, 6]. In addition, complementary and alternative medicine may be an option for patients with LHIVD, and the use of herbal medicine, cupping, manipulation, and various types of acupuncture has increased [7, 8].

In particular, thread-embedding acupuncture (TEA) involves embedding absorbable foreign substances, such as catgut and polydioxanone sutures, into acupoints using needles. The technique utilizes long-term stimulation, unlike traditional acupuncture [9]. Embedding a foreign substance also adds chemical stimulation to the mechanical stimulation of traditional acupuncture [10]. TEA has been used to treat a variety of diseases, including obesity [11], allergic rhinitis [12], facial palsy [13], and LHIVD. Although several recent randomized clinical trials (RCTs) have reported that TEA has a more favorable therapeutic effect on LHIVD than other types of acupuncture or other treatments, the evidence remains limited because these trials used poor assessment methods and had a high risk of bias [14].

To establish the clinical evidence regarding the efficacy and safety of TEA in the treatment of LHIVD, we will compare TEA with a sham control in a rigorously designed, full-scale RCT protocol that includes data on pain, function, and quality of life (QoL).

## Methods/design

### Trial design

This clinical study is a multicenter, randomized, patient–assessor blinded, sham-controlled trial with two parallel arms (1:1 ratio). The trial will take place at the Kyung Hee University Hospital, Gangdong (KHUHGD), Kyung Hee University Medical Center (KHUMC), Dongguk University Bundang Oriental Hospital (DUBOH), and Daegu Korean Medicine Hospital of Daegu Haany University (DKMHDHU). The efficacy and safety of TEA in patients with LHIVD will be evaluated by comparison with sham TEA (STEA) (Fig. 1).

**Fig. 1 Fig1:**
[figure not shown]
Study flowchart

The protocol of this study has been approved by the Institutional Review Boards (IRBs) of the institutions (KHUHGD: KHNMCOH 2016-09-006, KHUMC: 161216-HR-006, DUBOH: 2016–0012, DKMHDHU: DHUMC-D16015-PRO-02). The trial has also been registered at clinicaltrials.gov, which is a website of the United States National Institutes of Health (registration number: NCT03236753), as well as with the Clinical Research Information Service of the Republic of Korea (registration number: KCT0002439). All research procedures comply with Korean Good Clinical Practice (KGCP) and the Declaration of Helsinki. The methodology was established in accordance with the Consolidated Standards of Reporting Trials (CONSORT) [15], as well as with the revised Standards for Reporting Interventions in Clinical Trials of Acupuncture (STRICTA) [16]. Standard Protocol Items: Recommendations for Interventional Trials (SPIRIT) checklist is attached as Additional file 1 [17].

### Participants

The inclusion criteria for this study are as follows: (1) men or women aged 19–70 years; (2) radiating pain combined with abnormality on the lumbar spine that is more severe than bulging, as shown by computed tomography or magnetic resonance imaging [18, 19]; (3) ≥ 40 mm pain intensity on the 100-mm pain visual analogue scale (VAS) for lower back pain; and (4) agreement to participate and signing of the informed consent form after a detailed explanation of the clinical trial.

Participants who have the following characteristics will be excluded: (1) congenital abnormalities or surgical history in the lumbar region; (2) red flag signs that may indicate *cauda equina* syndrome, such as bladder and bowel dysfunction or saddle anesthesia; (3) tumor, fracture, or infection in the lumbar region; (4) injection in the lumbar region within one week of the trial start; (5) psychiatric disorder currently being treated, such as depression or schizophrenia; (6) inappropriate conditions for TEA due to skin disease or hemostatic disorder (prothrombin time with an international normalized ratio > 2.0 or treatment using an anticoagulant); (7) other diseases that could affect or interfere with therapeutic outcomes, including severe gastrointestinal disease, cardiovascular disease, hypertension, diabetes, renal disease, liver disease, or thyroid disorder; (8) contraindications for acetaminophen, including concurrent disease, hypersensitivity reaction, or other medication; (9) pregnancy or other inappropriate condition for TEA; (10) heavy drinking (> 3 glasses per day), which can cause hepatotoxicity when combined with acetaminophen [20].

### Procedure

Seventy participants with LHIVD will be recruited at four sites, each of which will recruit an appointed number of patients (KHUHGD: 18, KHUMC: 18, DUBOH: 18, DKMHDHU: 16). All participants who can read and write in Korean will be informed that they may voluntarily participate and that they can withdraw their consent at any stage. They will also be given essential information regarding the study protocol, including purpose, selection of participants, interventions by random allocation, schedule, expected benefits and risks, alternative treatment options, and confidentiality. Those who agree and sign the informed consent form will be screened through the assessment of demographics, medical history, present illness, vital sign, pregnancy test, and laboratory test. If they meet the eligibility criteria, the participants will be randomly allocated to the TEA group or STEA group. After random allocation, 10 visit sessions for treatment and assessment will be conducted according to an appointed 16-week schedule (Fig. 2).

**Fig. 2 Fig2:**
[figure not shown]
Standard Protocol Items: Recommendations for Interventional Trials (SPIRIT) figure. TEA thread-embedding acupuncture, STEA sham thread-embedding acupuncture, VAS visual analogue scale, ODI Oswestry Disability Index, RMDQ Roland-Morris disability questionnaire, EQ-5D-5 L EuroQol 5 Dimensions 5 Levels, GPE global perceived effect

### Interventions

In both groups, the intervention will be administered once a week for eight weeks using either a 29-gauge, 40-mm or a 29-gauge, 60-mm TEA or STEA needle (Hyundae Meditech, Wonju, South Korea). The treatment will be applied on 23 predefined acupoints according to STRICTA (Table 1). After sterilization of the skin surface, participants will be administered TEA in a prone position. In the STEA group, thread-removed TEA will be used instead of normal TEA. The thread will be removed aseptically and secretly to prevent infection and ensure patient-blinding, respectively.

**Table 1 Tab1:** Details of TEA treatment using the STRICTA 2010 checklist

Item	Detail
1. Acupuncture rationale	1a. Style of acupuncture: Thread-embedding acupuncture (TEA)
	1b. Reasoning for treatment provided (based on historical context, literature sources, and/or consensus methods, with references where appropriate): By the consensus of a group of clinical experts, based on a previous study [21–24]
	1c. Extent to which treatment was varied: Using bilateral EX-B2 of the herniated intervertebral disc its upper and lower levels
2. Details of needling	2a. Number of needle insertions per subject per session: 23 acupoints
	2b and 2c. Names of points used and depth of insertion, based on a specified unit of measurement, or on a particular tissue level: Bilateral EX-B2 of the level of the herniated intervertebral disc: perpendicular insertion (4 cm) Bilateral EX-B2 of the upper level of the herniated intervertebral disc: perpendicular insertion (4 cm) Bilateral EX-B2 of the lower level of the herniated intervertebral disc: perpendicular insertion (4 cm) Bilateral BL24: transverse insertion towards the L1 level along the erector muscle of the spine (6 cm) Bilateral BL25: transverse insertion towards the iliac crest (4 cm) Bilateral BL26: transverse insertion towards the L1 level along the erector muscle of spine (6 cm) Bilateral BL26: oblique insertion towards the iliolumbar ligament (6 cm) Bilateral EX-B7: oblique insertion towards the gluteus medius muscle (6 cm) Bilateral BL28: oblique insertion towards the sacroiliac ligament (6 cm) Bilateral GB30: perpendicular insertion (6 cm) Unilateral (symptomatic side) GB34, BL57, and ST36: oblique insertion towards the foot (4 cm)
	2d. Response sought: None
	2e. Needle stimulation: No additional stimulation
	2 f. Needle retention time: None
	2 g. Needle type: TEA (29-gauge × 40 mm, or 29-gauge × 60 mm)
3. Treatment regimen	3a. Number of treatment sessions: Eight
	3b. Frequency and duration of treatment sessions: Once a week for 8 weeks
4. Other components of treatment	4a. Details of other interventions administered to the acupuncture group: Rescue medication, lifestyle, education
	4b. Setting and context of treatment, including instructions to practitioners, and information and explanations to patients: Minimized conversation between practitioner and participant
5. Practitioner background	5. Description of participating acupuncturists: Specialists from the acupuncture and moxibustion department or residents supervised by a specialist with at least 3 years of clinical experience
6. Control or comparator interventions	6a. Rationale for the control or comparator in the context of the research question, with sources that justify this choice: Thread-removed TEA will be used as a comparator. In this way, the study focuses specifically on the existence of thread.
	6b. Precise description of the control or comparator. If sham acupuncture or any other type of acupuncture-like control is used (provide details as for Items 1 to 3 above): All conditions other than the use of thread-removed TEA will be the same as those in the treatment group.

*STRICTA* Standards for Reporting Interventions in Clinical Trials of Acupuncture, *TEA* thread-embedding acupuncture

The selection of acupoints and details of the procedure have been modified from similar studies [21–24] by a committee of Korean medicine doctors (KMDs) experienced in LHIVD and TEA. All therapeutic procedures will be performed by KMDs who have completed or have been taking a specialist acupuncture and moxibustion course for at least three years. To ensure homogeneity of intervention among the participating centers, all practitioners will undertake a training course together in advance.

### Rescue medication and concurrent treatment

Rescue medication will be provided to participants during the study period. If they feel severe pain (> 60 mm on the 100-mm VAS), they will be permitted to take up to 2600 mg/day (four 650-mg tablets) and 6500 mg/week (10 tablets) of acetaminophen (Suspen ER C.T.; 650 mg/tablet, Hanmi Pharm. Co., Ltd., Seoul, Republic of Korea). A clinical research coordinator (CRC) will educate the participants in keeping a medication diary; they will also check the returned medications. To precisely assess efficacy, rescue medicine will be prohibited within 24 h of a visit.

Other than rescue medication, all treatment that may affect the result will be restricted, including injections, surgical interventions, acupuncture, physical therapy, or drugs for pain control. Medications that the participants have been taking before the trial, or those that they take for other diseases or adverse events (AE), will be allowed at the discretion of the investigators depending on whether they affect the symptoms of LHIVD. Changes to concurrent treatments will be recorded at each visit.

### Outcomes

The primary outcome will be change in the intensity of lower back pain. The secondary outcomes will be intensity of radiating pain, functions of daily life, QoL, and global perceived effect (GPE). Additionally, all AEs will be recorded at each visit and assessment of blinding will be conducted at the end of the study. All assessments will be performed by independent researchers who are not involved in the scheduled intervention (Table 2).

**Table 2 Tab2:** Schedule for assessment

Outcome measures	Screening	Baseline	Treatment (weeks 1–8)		Follow-up (weeks 9–16)	
			Week 4	Week 8	Week 12	Week 16
VAS for lower back pain	◎	◎	◎	◎	◎	◎
VAS for radiating pain		◎	◎	◎	◎	◎
ODI		◎	◎	◎	◎	◎
RMDQ		◎	◎	◎	◎	◎
EQ-5D-5 L		◎	◎	◎	◎	◎
GPE			◎	◎	◎	◎
Assessment of binding						◎
Adverse events^a^		◎	◎	◎	◎	◎

^a^Adverse event will be monitored throughout the study period

*VAS* visual analogue scale, *ODI* Oswestry Disability Index, *RMDQ* Roland-Morris disability questionnaire, *EQ-5D-5 L* EuroQol 5 Dimensions 5 Levels, *GPE* global perceived effect

### Primary outcome measure

The intensity of lower back pain will be evaluated using the 100-mm VAS [25]. At pre-trial screening, at weeks 1 (baseline), 4, and 8 (primary endpoint), and at weeks 12 and 16 (follow-up sessions), participants will be asked to record their pain intensity within the past week on a 100-mm linear scale (0, absence of pain; 100, worst pain imaginable). Change from baseline after eight sessions of treatment will be compared between the groups as the primary outcome.

### Secondary outcome measures

#### 100-mm VAS for radiating pain

The intensity of radiating pain of the lower extremities will also be assessed using a 100-mm VAS at pre-trial screening and at weeks 1, 4, 8, 12, and 16.

#### Oswestry Disability Index

Inability to function in daily life due to lower back pain will be assessed using the ODI [26] at weeks 1, 4, 8, 12, and 16. The ODI questionnaire consists of 10 sections: pain; personal care; lifting; walking; sitting; standing; sleeping; sex life; social life; and traveling. Each question is scored from 0 to 5; the total score is calculated as a percentage disability.

#### Roland-Morris disability questionnaire

Dysfunction in daily life will be assessed using the Roland-Morris disability questionnaire (RMDQ) at weeks 1, 4, 8, 12, and 16. The RMDQ contains 24 sentences that people have used to describe themselves when they have lower back pain. Participants check the sentences that they think best describe their life on that day; the score is the total number of sentences checked (from 0 to 24) [27].

#### EuroQol 5 Dimensions 5 Levels

The patients’ QoL and general health status will be assessed using the EuroQol 5 Dimensions 5 Levels (EQ-5D-5 L) at weeks 1, 4, 8, 12, and 16. The EQ-5D-5 L essentially consists of the EQ-5D descriptive system and EQ VAS. The EQ-5D descriptive system comprises five dimensions: mobility; self-care; usual activities; pain/discomfort; and anxiety/depression. Each dimension is rated from 1 to 5 (1, no problems; 2, slight problems; 3, moderate problems; 4, severe problems; 5, extreme problems). The EQ VAS scale can be used to assess a patient’s current health status. It is a 20-cm scale numbered from 0 to 100 (0, the worst health they can imagine; 100, the best health they can imagine) [28].

#### Global perceived effect

The subjective effects of the treatments will be assessed using the GPE at weeks 4, 8, 12, and 16. The participants will score their perceived change using a 7-point scale (1, worst ever; 2, much worse; 3, worse; 4, not improved and not worse; 5, improved; 6, much improved; 7, best ever) [29].

#### Assessment of blinding

At the end of the study, the researchers will assess the appropriateness of the patient-blinding method by asking the participants which group they think they belong to. The answer can take three forms as follows: “TEA;” “STEA;” or “do not know.” The blinding index (BI) will be calculated using James’ method based on the answer. The BI increases from 0 to 1 with the success of patient-blinding (0, total lack of blinding; 0.5, completely random; 1, complete blinding) [30, 31].

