## Discussion

This RCT will be conducted in a rigorous, sham-controlled setting to investigate the therapeutic effects of TEA. TEA has been reported to have beneficial effects on musculoskeletal diseases such as ankylosing spondylitis [33], chronic pelvic pain [34], and cervical spondylosis [35], and a review study on the use of TEA to treat LHIVD reported that 17 RCTs had positive results. However, these RCTs had a high risk of bias, especially in terms of blinding, because they used an active control [14]. TEA differs from traditional acupuncture because it involves both chemical and mechanical stimulation using embedded substances. Therefore, sham controls using thread-removed TEA are appropriate in attempting to discover whether the treatment has any unique effects.

To blind patients, the thread will be removed from the needles in a sterile manner with the help of an assistant. In this way, the patients will not see the thread removal. This method was found by Yoo et al. to be safe [36]. However, it will also be necessary to verify whether the blinding has actually worked. Furthermore, to blind the assessors, pre-assigned independent assessors will refrain from conversations with the practitioners that are unrelated to the evaluation. All data will be organized and analyzed by an independent statistician in accordance with the study protocol.

The TEA procedure and the selection of acupoints were decided by the consensus of a committee of clinical experts, with reference to former RCTs [21–24] and specified whole details, as prescribed in the STRICTA form. To standardize the procedures, details of the acupuncture, including size, acupoints, direction, sessions, frequency, and duration are specified in the protocol and will be communicated to all practitioners, who are acupuncture specialists, in a preliminary meeting for practice. All researchers participating in this study also completed the KGCP training course from the certificated institution of the Korean Ministry of Food and Drug Safety.

The results of this study will yield clinical evidence comparing TEA to needle-only acupuncture by providing data about subjective changes in lower back pain, radiating pain, global function, and QoL in patients with LHIVD over time. These findings will help clinicians to understand TEA and utilize the treatment as a therapeutic option for patients with LHIVD.

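### Blinding is asked only at week 16 and summarised only by a pooled James index, which can read as random while one arm guesses its allocation well above chance

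*Protocol article*

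**What the plan says.** Timing: the section on assessment of blinding places the question once, when the study ends: "At the end of the study, the researchers will assess the appropriateness of the patient-blinding method by asking the participants which group they think" (that is, each patient's own guess at the allocation). Table 2 agrees. Its row, printed as "Assessment of binding" and plainly meaning blinding, has a single mark, under week 16.

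Index: there are three possible answers (TEA, STEA or don't know), and "The blinding index (BI) will be calculated using James’ method based on the answer". The protocol explains the scale as 0 for no blinding, 0.5 for random guessing and 1 for complete blinding. It names no by-arm index and no cut-off for adequacy.

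Treatment and endpoint: under Interventions, "the intervention will be administered once a week for eight weeks". The primary outcome section sets the VAS "at weeks 1 (baseline), 4, and 8 (primary endpoint), and at weeks 12 and 16 (follow-up sessions"), and "participants will be asked to record their pain intensity within the past week on a 100-mm linear scale". The Discussion adds: "However, it will also be necessary to verify whether the blinding has actually worked".

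**The concern.** The primary outcome is the patient's own pain rating, so the comparison depends heavily on patients not knowing their arm. The arms differ in one thing, thread left in the tissue, and it is left in one arm only. The Background describes that thread as a longer-lasting mechanical and chemical stimulus. The safeguards under Blinding (prone position, little conversation, separate appointments) deal with what patients see or hear. They do not deal with what patients might feel. A failure confined to one arm is therefore the pattern the check most needs to detect.

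Two stated choices weaken the check. The question comes well after the endpoint it should inform. The index also averages over the arms and gives full credit to don't-know answers. The reader of the results could be left with one reassuring number that does not show how each arm guessed.

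**Working it through.** **Timing.** Sessions are weekly for eight weeks, so the last falls at about week 8, which is also the primary endpoint. The blinding question is at week 16, and 16 - 8 = 8 weeks later. By then each patient is scheduled to have given four post-baseline VAS scores and four global perceived effect ratings (weeks 4, 8, 12 and 16).

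**Inputs.** 35 patients per arm (Sample size section); three answers and anchors 0 / 0.5 / 1 (Assessment of blinding). The guess counts are assumptions, because the protocol gives none; a range is shown.

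**Formulas.**
- James: BI = [1 + P_DK + (1 - P_DK)K]/2, with K = (P_Do - P_De)/P_De. P_DK is the share of don't-know answers. P_Do = 0.5 × wrong guesses / definite guesses. P_De is the same quantity expected from the margins of the definite guesses.
- Bang, per arm: (correct - wrong)/n, with SE = √{[p_c + p_w - (p_c - p_w)²]/n}, where p_c and p_w are the shares correct and wrong.

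**The protocol's anchors reproduce.** All correct: P_DK = 0, K = -1, BI = 0. Random guessing: P_DK = 0, K = 0, BI = 0.5. All don't know: BI = 1.

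**Pattern A: TEA 18/3/14, STEA 11/10/14.**
- P_DK = 28/70 = 0.40; P_Do = 0.5 × 14/42 = 0.167.
- P_De = 0.5 × (21×13 + 21×29)/42² = 0.25; K = -0.333.
- BI = (1 + 0.40 - 0.60 × 0.333)/2 = 0.60.
- Bang TEA = (18 - 3)/35 = +0.43, SE 0.109; Bang STEA = (10 - 11)/35 = -0.03.

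**Pattern B: TEA 28/2/5, STEA 7/7/21.**
- P_DK = 26/70 = 0.371; P_Do = 0.5 × 9/44 = 0.102.
- P_De = 0.5 × (30×9 + 14×35)/44² = 0.196; K = -0.479.
- BI = (1 + 0.371 - 0.629 × 0.479)/2 = 0.54.
- Bang TEA = (28 - 2)/35 = +0.74, SE 0.093; Bang STEA = (7 - 7)/35 = 0.00.

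Two further patterns are worked the same way. James intervals are from a multinomial bootstrap; Bang intervals are ±1.96 SE.

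| Pattern | TEA arm | STEA arm | James (95%) | Bang TEA (95%) | Bang STEA |
|---|---|---|---|---|---|
| A | 18/3/14 | 11/10/14 | 0.60 (0.49 to 0.71) | +0.43 (0.21 to 0.64) | -0.03 |
| B | 28/2/5 | 7/7/21 | 0.54 (0.42 to 0.65) | +0.74 (0.56 to 0.93) | 0.00 |
| C | 28/7/0 | 10/10/15 | 0.49 (0.37 to 0.60) | +0.60 (0.33 to 0.87) | 0.00 |
| D | 28/7/0 | 28/7/0 | 0.50 (0.41 to 0.59) | +0.60 (0.33 to 0.87) | -0.60 |

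**Do the answers differ by arm?** Pearson chi-square on the 2×3 table, 2 df:
- A: 2 × (3.5²/14.5 + 3.5²/6.5 + 0) = 5.46, p = 0.065.
- B: 2 × (10.5²/17.5 + 2.5²/4.5 + 8²/13) = 25.2, p < 0.0001.
- C: 2 × (9²/19 + 1.5²/8.5 + 7.5²/7.5) = 24.1, p < 0.0001.
- D: identical answers, chi-square 0.

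C and D have almost the same James value (0.49 and 0.50). In C the answers depend strongly on the arm; in D they carry no information about it. Only the by-arm figures separate the two.

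**The case against.** The case for leaving the plan alone is substantial.

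- **The index.** James' index is an established method. The three-option answers also allow Bang's index, and by-arm tables are often left to an analysis plan, which is not shown here. This makes the remedy easy, but the article still fixes one time point and one pooled summary, and those can be judged.
- **Certification.** A reader might infer that the check would certify failed blinding. The documents do not support that. They give anchors but no cut-off, and no decision depends on the index.
- **Unblinding.** A reader might take pattern A as proof of an unblinded TEA arm, or its James value as better than random. Neither follows. The counts are assumed, the James interval includes 0.5, and the arm-by-answer test gives p = 0.065 (Fisher on definite guesses only, p = 0.043). A high TEA-arm index can also reflect expectation or perceived benefit, as pattern D shows. Nor does the protocol say that patients can feel the thread.
- **Timing.** A week-8 guess is also coloured by how the patient has done, and asking last avoids raising allocation before the week-12 and week-16 outcomes. Both points stand. It would also be too strong to say that a week-16 answer tells nothing about week 8, since a patient who recognised the treatment during the sessions may well still say so. Nor do the documents say whether patients who withdraw are asked, so it cannot be asserted that dropouts are missing from the check.

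**Conclusion.** The point holds in a limited form. The week-16 question comes eight weeks after the primary endpoint and is a weak proxy for belief when the primary VAS was marked. James' index alone cannot show whether one arm guesses well above chance. In the three assumed patterns where only the TEA arm guesses well (Bang +0.43 to +0.74, sham about 0), James lies between 0.49 and 0.60, which the protocol's own scale reads as about random or better.

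This rests on assumed guess counts with 35 answers per arm, and on reading adequacy against the 0.5 anchor because no cut-off is stated. It shows that the summary can mislead. It does not show that blinding will fail or that the planned index would be taken as proof of success. The sample size and the primary test do not change.

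**What to change.** 1. Report the guess counts by arm and Bang's index by arm with 95% confidence intervals, beside James' index. The planned answers already suffice, so this costs a few lines of analysis and can be done even if data collection has finished (the article estimated completion by 30 June 2018).
2. Read the TEA-arm index together with the sham-arm index. High in TEA with a mirror-image negative value in sham suggests expectation. High in TEA with about zero in sham means the answers differ by arm, though perceived benefit remains a possible reason.
3. Where still possible, ask the same question at the week-8 visit, after the VAS, and keep week 16. This adds one question at an existing visit. The downside is that it may prompt patients to think about allocation before the week-12 and week-16 outcomes. If it is no longer possible, report the timing as a limitation.
4. A question after an early session, and a table of the week-8 VAS difference by guess, are optional. Any such table should be labelled exploratory, because the guess may itself follow from the outcome.
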